## Abstract

**Background:**

Globally, the prevalence of type 1 diabetes mellitus (T1DM) is rising. In 2020, a total of 124,652 Australians had T1DM. Maintaining optimal glycemic control (hemoglobin A_1c_ ≤7.0%, ≤53 mmol/mol) on a standard carbohydrate diet can be a challenge for people living with T1DM. The Diabetes Complications and Control Trial established that macrovascular and microvascular complications could be reduced by improving glycemic control. Recent studies have found that a very low or low carbohydrate diet can improve glycemic control. However, the overall evidence relating to an association between a very low or low carbohydrate diet and glycemic control in people living with T1DM is both limited and mixed. In addition, research has suggested that a reduced quality of life due to anxiety and depression adversely influences glycemic control. Despite a potential link between a very low or low carbohydrate diet and optimal glycemic control, to our knowledge, no research has examined an association between a low carbohydrate diet, quality of life, and glycemic control, making this study unique in its approach.

**Objective:**

The study aims to develop a validated diabetes-specific quality of life questionnaire for use in Australian adults with T1DM and to determine if an association exists between a low carbohydrate diet, quality of life, and glycemic control in Australian adults living with T1DM.

**Methods:**

This cross-sectional study will be conducted in a tertiary hospital outpatient setting and will consist of 3 phases: phase 1, online Australian diabetes-specific quality of life questionnaire development and piloting (25-30 adults with T1DM); phase 2, questionnaire validation (364 adults with T1DM); and phase 3, a 12-week dietary intervention to determine if an association exists between a low carbohydrate diet, quality of life, and glycemic control in adults with T1DM (16-23 adults with T1DM). The validation of the study-developed Australian diabetes-specific quality of life questionnaire, and changes in hemoglobin A_1c_ and quality of life in adults with T1DM while undertaking a low carbohydrate diet over 12 weeks will be the primary outcomes of this study.

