#### Study Phase 3: The Low Carbohydrate Dietary Intervention

A sample size of 16 has been calculated with a 0.05 significance level and power of 0.8 to detect a significant clinical difference of 1.0% in HbA_1c_. A 1.0% change in HbA_1c_ will be used because dietary changes alone have shown to improve HbA_1c_ by 1.0% [60]. To complete the study, 16 participants are required. To account for a 40% attrition rate [12], 23 participants will be the maximum number recruited.

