### Outcomes

The primary outcomes will be divided according to the study phases. Primary outcome 1 will be related to the development and piloting of the new Australian diabetes-specific QoL questionnaire in study phase 1. Primary outcome 2 will be related to the validation of the study-developed questionnaire in study phase 2. Study phase 3 will produce 3 subdeliverables that will examine the association between a low carbohydrate diet and glycemic control in adults with T1DM (primary outcome 3.1), examine the association between a low carbohydrate diet and QoL in adults with T1DM (primary outcome 3.2), and investigate whether a low carbohydrate diet mediates the relationship between QoL and glycemic control in adults with T1DM (primary outcome 3.3).

This study will have no secondary study outcomes.

Figure 1 schematically shows the relationship between the study objectives. The association between QoL, low carbohydrate diet, and glycemic control variables have been represented with double-headed arrows. This indicates that the direction of the association is unclear and may be bidirectional in nature, as each variable has the potential to influence the other [13,19,30].

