## Discussion

This study is the first of its kind to examine the association between a low carbohydrate diet, QoL, and glycemic control. This cross-sectional study protocol aims to develop, pilot, and validate a diabetes-specific QoL questionnaire and determine if an association exists between QoL and glycemic control while using a low carbohydrate dietary intervention in Australian adults living with T1DM.

The strengths of this study are that, to our knowledge, no previous published research has evaluated a low carbohydrate diet and its influence on QoL and glycemic control in Australian adults living with T1DM. Moreover, this is the first study to develop and validate an Australian T1DM-specific QoL questionnaire Therefore, the strengths of this study are its unique approach.

The potential limitations of this study include the fact that, first, the Australian diabetes-specific QoL questionnaire is not available to those who are vision impaired, intellectually impaired, or have any other type of diabetes, such as T2DM and gestational diabetes mellitus. Future studies could develop resources to include these populations. Second, in study phases 1 and 2, questionnaire data will be self-reported and may have the potential to produce social desirability bias [73]. However, using self-reported data is the most feasible option for this pilot study in order for the sample size (N=364) and statistical validation of the questionnaire to be achieved. Third, study phase 3 has been designed as a nonrandomized intervention group pilot study that will inform the design and feasibility of a potential larger randomized control trial. Finally, in study phase 3, there is potential selection bias: individuals who are highly motivated to improve glycemic control are more likely to participate [25].

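### Phase 3 primary outcomes are stated inconsistently: 12-week changes in HbA1c and QoL in the abstract, but associations plus mediation in the Outcomes section and Table 4

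*Protocol article*

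**What the plan says.** Besides validation of the questionnaire, the Methods paragraph of the abstract lists "changes in hemoglobin A_1c_ and quality of life in adults with T1DM while undertaking a low carbohydrate diet over 12 weeks" as primary. For Phase 3 that is two outcomes, each a change with a time frame.

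The Outcomes section gives three for Phase 3. The first is to "examine the association between a low carbohydrate diet and glycemic control in adults with T1DM (primary outcome 3.1"). The second (3.2) has the same form with QoL in place of glycemic control. The third is to "investigate whether a low carbohydrate diet mediates the relationship between QoL and glycemic control in adults with T1DM (primary outcome 3.3"). The section then states that there are no secondary outcomes, so all three are primary. For these outcomes it names neither HbA1c, nor a change from baseline, nor 12 weeks.

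Table 4 carries 3.1 to 3.3 with one identical analysis entry: ANOVA and correlations at the bivariate level, then hierarchical regression adjusted for sociodemographic factors. The independent variable is the low carbohydrate diet in all three rows.

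The Sample Size section justifies 16 completers in Phase 3 as enough "to detect a significant clinical difference of 1.0% in HbA_1c", with a significance level of 0.05 and power of 0.8. No other Phase 3 outcome is sized. The data analysis paragraph for Phases 2 and 3 sets P<.05 and gives no ranking or split.

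**The concern.** A mean within-person change and an association across people are different quantities. Each can be present without the other. Mediation is a third question, which neither of the first two answers. If the article calls one set primary in one place and another set primary elsewhere, a reader of the results cannot tell which finding Phase 3 was set up to deliver, or which finding the stated power supports.

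The design sharpens this. Phase 3 has a single group, all on the prescribed plan, with HbA1c and the questionnaire taken once before and once after. What such a design estimates directly is a pre-post change, and Table 4 does not name one.

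**Working it through.** **1. The four places side by side (Phase 3 only)**

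| Place | Quantity | HbA1c named | Change named | 12 weeks named | Mediation |
|---|---|---|---|---|---|
| Abstract, Methods | change in HbA1c; change in QoL | yes | yes | yes | absent |
| Outcomes | association (3.1, 3.2); mediation (3.3) | no | no | no | primary |
| Table 4 | ANOVA, correlations, regression on diet | no | no | no | listed |
| Sample Size | 1.0% difference, called a change in the next sentence | yes | yes | no | absent |

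The abstract and the Sample Size section agree with each other. So do the Outcomes section and Table 4. The two pairs do not agree.

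**2. What diet can mean as an independent variable.** With one group on one plan, there are two readings.
- Diet stands for the visit (before or after). ANOVA is then a pre-post comparison. With two time points, repeated-measures ANOVA is the paired t test.
- Diet stands for recorded intake, since the food diaries are to be used in the analysis. Correlation and regression then ask whether people who ate less carbohydrate differ in glycemic control or QoL.

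Table 4 lists methods for both readings without ranking them.

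**3. How far the two quantities can part.** The documents do not say which variables would be correlated, so this is for scale only. For any Pearson correlation with n = 16, two-sided 0.05:
- t(0.975, 14) = 2.145
- critical |r| = 2.145 / √(14 + 2.145²) = 0.497

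A correlation of about 0.50 is therefore significant whatever the mean change is. A mean fall of 1.0% can equally occur with r near 0.

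**4. The plan's own figure, N = 16.** The SD, the test and the sidedness are not stated, so 16 can be neither reproduced nor refuted, only back-solved for the SD:
- One-sample (paired) t, two-sided 0.05, power 0.80, n = 16: standardised effect 0.749, so SD of change = 1.0 / 0.749 = 1.33.
- The same test, one-sided: 1.0 / 0.652 = 1.53.
- Two-group normal formula, 16 per arm: 1.0 / ((1.960 + 0.842) × √(2/16)) = 1.01. This does not match a single group.

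The first is an assumption, not a figure from the protocol. On any of them the calculation concerns HbA1c only.

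**5. Testing each Phase 3 primary at 0.05, independence assumed**
- Two outcomes (abstract): 1 − 0.95² = 9.75%.
- Three outcomes (Outcomes section): 1 − 0.95³ = 14.3%.

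Under the two-sided assumption in step 4, a Bonferroni split would lower power for HbA1c from 80% to about 69% (alpha 0.025) or 62% (alpha 0.0167).

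**The case against.** The best reply is that changes are the measurements and association is the objective. The abstract itself describes Phase 3 as looking for an association and in the next sentence names changes as outcomes. HbA1c and the questionnaire are collected only at the two visits, and the Introduction says glycemic control is evaluated by HbA1c. On this reading 3.1 and 3.2 are the abstract's two changes in looser words. That is a fair reading and may be what was meant. Two things limit it. Table 4 adds correlations and regression, which do not estimate a mean change. And 3.3 cannot be read as a change in HbA1c or QoL, so its primary status remains unmatched in the abstract.

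A second reply is that Phase 3 is described as a nonrandomized pilot to inform a larger trial, so no single result has to decide anything. That lowers the stakes. It does not remove the contradiction, because the article still claims primary outcomes, a significance threshold and a power.

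Some stronger readings are tempting but not supported:
- A reader might count three primary outcomes against five across the whole study. The extra non-Phase 3 item is questionnaire development, a qualitative Phase 1 deliverable with no bearing on what Phase 3 tests.
- A reader might take the Discussion's wording, "determine if an association exists between QoL and glycemic control while using a low carbohydrate dietary intervention", as a third list. It paraphrases the study aim and follows a sentence that names all three variables.
- A reader might infer that the authors intend to report whichever version is significant. Nothing shows this, and the full protocol and analysis plan are not at hand.

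**Conclusion.** The inconsistency stands, and it is confined to Phase 3. The certain part is mediation, which is primary in the Outcomes section and absent from the abstract's list. The probable part is that 3.1 and 3.2 are imprecise wording for the 12-week changes, made worse by an analysis table that names no pre-post change. The stated power belongs to HbA1c alone; QoL, correlation and mediation have none.

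Reconciling the lists would not by itself settle which result decides Phase 3. The abstract alone already has two unranked primary outcomes, so the ranking must be stated as well.

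The text comparison needs no assumption. The SD of 1.33 rests on an assumed two-sided one-sample t test, and the error rates in step 5 rest on independence. They show scale and do not carry the finding. The point should be corrected before Phase 3 is analysed, and the correction is mainly one of wording.

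**What to change.** - Use one Phase 3 list in the abstract, the Outcomes section and Table 4.
- Define 3.1 as the within-person change in HbA1c and 3.2 as the within-person change in the questionnaire score. Both run from the preintervention to the postintervention visit, and each is analysed as a paired pre-post change.
- Name HbA1c change, the outcome Phase 3 is sized on, as the deciding outcome or as first in a fixed testing order with QoL second. A fixed order keeps the full 0.05 for HbA1c and so leaves the planned power intact.
- Report mediation and the correlation and regression analyses as exploratory, with confidence intervals. State for each which variable represents diet.

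The cost is wording in those three places, and mediation loses primary status. No data collection or sample size changes. The study can keep its stated interest in association as an aim, with the changes as the primary measures of it.

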**Results:**

Phase 1 of the study is currently open for recruitment and has recruited 12 participants to date. It is anticipated that the first results will be submitted for publication in November 2021. Presently, no results are available.

**Conclusions:**

This study is the first of its kind in that it will be the first to generate a new validated instrument, which could be used in evidence-based practice and research to understand the quality of life of Australian adults with T1DM. Second, the low carbohydrate dietary intervention outcomes could be used to inform clinicians about an alternative approach to assist T1DM adults in improving their quality of life and glycemic control. Finally, this study could warrant the development of an evidence-based low carbohydrate dietary guideline for adults living with T1DM with the potential to have a profound impact on this population.

**Trial Registration:**

ClinicalTrials.gov NCT04213300; https://clinicaltrials.gov/ct2/show/NCT04213300

**International Registered Report Identifier (IRRID):**

PRR1-10.2196/25085

## Introduction

There are more than 420 million people worldwide, aged 20 to 79 years, living with type 1 diabetes mellitus (T1DM) [1]. In 2020, a total of 124,652 Australians had T1DM [2]. As the number of people with this autoimmune condition increases, so does the prevalence of those with suboptimal glycemic control [3].

Glycemic control is evaluated by glycated hemoglobin (HbA_1c_), which provides an average blood glucose level over a period of 2 to 3 months [4]. The target for optimal glycemic control for people with T1DM is ≤7.0% (≤53 mmol/mol) [5]. In 2015, data from T1DM registries from 19 countries across Europe, North America, and Australasia (N=324,501) showed that only 46% of adults (aged ≥25 years) with T1DM achieved the HbA_1c_ target of <7.0% [6].

Suboptimal glycemic control increases the risk of development and progression of various diabetes-related complications including hypoglycemia, diabetic ketoacidosis neuropathy, nephropathy, retinopathy, and cardiovascular disease [1].

The Diabetes Control and Complications Trial aimed to determine the long-term frequency and severity of chronic complications in individuals living with T1DM using intensive insulin therapy with the goal of maintaining blood glucose levels as close to normal range as possible. This seminal work convincingly demonstrated the effectiveness of intensive insulin therapy in reducing the long-term complications of T1DM and improving the prospects for a healthy life span for individuals living with T1DM. This landmark study established the glycemic control guidelines used today [7].

A recent systematic review reported the incidence and prevalence of diabetic ketoacidosis in adults with T1DM from 3 continents [8]. In this review, 19 studies (1 randomized control trial and 18 cross-sectional studies) containing similar numbers of males and females, were included, with over 80% of participants being White. The review found that adults aged 18 to 25 years had the highest prevalence of diabetic ketoacidosis (100-120 cases per 1000 in studies with 12 months’ recall) compared to those older than 65 years who had the lowest prevalence of diabetic ketoacidosis (38-60 cases per 1000 in studies with a 12-month recall) [8].

Traditionally, it has been recommended that people living with T1DM consume 45% to 60% of total energy intake from carbohydrate sources [9]. Dietary approaches commonly used to manage glycemic control include carbohydrate counting, which matches insulin-to-carbohydrate intake, and/or a low glycemic index diet [10,11].

Recently, there has been a growing focus on the utility of a low carbohydrate diet to manage glycemic control in individuals living with T1DM [12,13]. This dietary management strategy has been thoroughly investigated in people living with type 2 diabetes mellitus (T2DM) [14,15]. However, there is a paucity of evidence regarding T1DM.

A very low carbohydrate diet is defined as 0-50 g per day or <10% of the total daily energy intake [16], while a low carbohydrate diet is defined as <130 g per day or <26% of the total daily energy intake [16,17]. Schmidt et al [12] conducted a randomized crossover study to examine the effects of a low carbohydrate diet (<100 g carbohydrate/day) compared to a high carbohydrate diet (>250 g carbohydrate/day) on glycemic control. Participant baseline characteristics included White adults from Denmark (male: 6/14, 43%; female: 8/14, 57%; 14 with T1DM; mean age 44 years, SD 12 years). Participant median diabetes duration was 19 (range 13-32) years, and the HbA_1c_ was 7.5% (range 7.2%-7.6%). Participants undertook two, 12-week interventions separated by a 12-week “washout” period, with 10 of the 14 participants completing the study. The study found that a low carbohydrate diet compared to a high carbohydrate diet did not significantly improve HbA_1c_, but did stabilize glucose variability and reduce hypoglycemia frequency (*P*<.001) [12].

There is only 1 systematic review that has examined the association between very low and low carbohydrate diets and glycemic control in people living with T1DM [18]. It included a total of 9 original studies: 2 randomized controlled trials [19,20], 2 quasi pre– or post–cross-sectional [21,22] studies, 4 case series [23-26], and 1 case report [27]. Participants ranged from 14 to 65 years of age and resided in the United Kingdom, the United States, Europe, Australia, or New Zealand. Fewer than half the studies (3/9) reported a significant improvement in HbA_1c_ (0.7%-2.4%; *P*<.05) [18]. The difference in sample sizes, study methodologies, and participant baseline characteristics (age, gender, ethnicity, and diabetes duration) may account for these nonsignificant results. Despite a paucity of evidence, associations have been observed between very low and low carbohydrate diets with good glycemic control in individuals living with T1DM [13,19,23-26]. However, these findings are relatively mixed [12,13,19,21,23-26,28-31].

Very little research has been conducted in the area of a low carbohydrate diet and quality of life (QoL) in adults living with T1DM. Additional research is needed to determine if there is a link between these 2 variables because T1DM has been reported to be the cause of a reduced QoL [32]. Roy and Lloyd [33] conducted a systematic review to examine the evidence for rates of depression within the diabetes population. The authors reported the prevalence of depression to be 3 times higher in people living with T1DM when compared to those without it (12% vs. 3%, respectively). In Australia, it has been found that 41% of adults (>18 years old) living with T1DM experience diabetes-related anxiety, depression, and stress [34]. In turn, these psychological issues have been linked with suboptimal glycemic control and diabetes complications, thus contributing to diminished QoL.

There is no agreed explanation of QoL [35,36] as demonstrated by the numerous existing definitions reported in the literature [36-40]. There is however, universal agreement that QoL is a multidimensional, subjective construct that includes at least three domains: physical (eg, pain), psychological (eg, body image), and social (eg, relationships) well-being [35-37,41-44]. Common QoL definitions do not appear to use a holistic lifestyle approach and fail to consider dietary well-being, a key aspect of QoL for individuals living with T1DM [45].

QoL is commonly assessed in T2DM populations [46,47] but rarely in adults living with T1DM [48]. Pereira et al [47] conducted a systematic review to determine the relationship between QoL and HbA_1c_ in those living with T1DM. The review consisted of 110 studies (78 observational and 32 interventional) from countries in North America and Europe, and included 69 T1DM studies, 35 T2DM studies, and 6 T1DM and T2DM studies. All studies included an approximately 1:1 male to female participant ratio, with an age range from 5 to 70 years and a diabetes duration from 2 to 29 years. QoL instruments used included the Diabetes Quality of Life Measure (DQOL) [49] and the Diabetes Quality of Life for Youth (DQOLY) measure [50]. Baseline HbA_1c_ for T1DM interventional and observational studies ranged from 6.1% to 11.0% and from 7.0% to 12.2%, respectively. Endpoint HbA_1c_ ranges for interventional and observational studies were reduced from 5.9% to 9.5% and from 7.1% to 9.6%, respectively. Despite a reduction in HbA_1c_, only 41% of participants reported an improvement in QoL, suggesting that people living with T1DM generally perceive this as unsatisfactory [47].

The Diabetes-Specific Quality of Life Scale (DSQOLS) is the only validated QoL instrument for adults living with T1DM [48]. Nevertheless, it is not suitable for assessing the dietary well-being of Australian adults because the instrument fails to consider carbohydrate counting, which is a fundamental skill used by those living with T1DM in Australia to manage insulin and blood glucose levels [51]. The instrument also neglects to assess food intake satisfaction, which is another important aspect of dietary well-being [45]. These factors are likely to influence QoL outcomes; therefore, the development of a new T1DM-specific QoL instrument that includes the four domains of physical, psychological, social, and dietary well-being is being proposed.

To address the identified deficit in the literature, our study aims to develop and validate a diabetes-specific QoL questionnaire for use in Australian adults with T1DM and to determine if an association exists between a low carbohydrate diet, QoL, and glycemic control.

## Methods

### Study Design and Ethics

This cross-sectional study will be conducted in 3 phases. Study phase 1 will include online Australian diabetes-specific QoL questionnaire development and piloting. Study phase 2 will consist of Australian diabetes-specific QoL questionnaire validation with the following 2 subphases: subphase 2a, which will include initial validation with an online diabetes-specific QoL questionnaire; study subphase 2b, which will include online questionnaire validation of the Australian diabetes-specific QoL, the Medical Outcomes Study 36-Item Short Form Health Survey (MOS SF-36), DQOL, and Problem Areas in Diabetes (PAID-20) questionnaires; study phase 3 will include intervention, which will be aimed at determining if an association exists between a low carbohydrate diet, QoL, and glycemic control in adults living with T1DM.

Ethics approval has been obtained from the Gold Coast Hospital and Health Service (GCHHS) Human Research Ethics Committee (HREC) and the University of Canberra HREC. Ethics approval numbers for study phase 1 and 2 are HREC/2019/QGC/54049 and HREC/2019/UC/2223, respectively. The approval numbers for study phase 3 are HREC/2019/QGC/60717 and HREC/2020/UC/4691. The study was registered at ClinicalTrials.gov (NCT04213300).

